### Data collection and outcomes

Starting in the spring of 2010, we will perform a retrospective data abstraction from the paper charts and/or electronic health records in each physician's office. For each patient, demographic information (including date of birth, sex and postal code of home residence) and clinical information (including diabetes duration, comorbidities, family history and baseline drug utilization) will be collected. Outcome measures will be assessed for each patient for the period between July 2009 and March 2010. The primary outcome will be that the patient is receiving a statin (as determined by the record of a new prescription, the record of a prescription renewal, or a notation that the patient is taking a statin). This outcome is selected because as a process of care outcome, it is closely linked to physicians' behaviour and hence is more likely to change as a result of the intervention, and because no more than one-third of patients currently receive statins, [13,22,23] so there is substantial opportunity for improvement.

The other process outcome that will be evaluated is whether the patient is receiving a prescription for an angiotensin-converting enzyme inhibitor or angiotensin receptor blocker. In addition, the following intermediate outcomes will also be collected:

• A1c

• Blood pressure

• LDL-cholesterol

• Total-/HDL-cholesterol ratio

• Body mass index

• Waist circumference

When there are multiple measurements for these intermediate measures for a patient, the last one during the observation period will be used.

We will also measure "clinical inertia"[24]. For each A1c, blood pressure or LDL-cholesterol reading that is above the recommended clinical practice guideline target, we will determine whether, at the next patient visit, there is notation in the chart of a recommended change: the addition of a new medication, a dose change for an existing medication, a dietary or physical activity recommendation, etc.

The data collection will be conducted using a laptop computer by a trained and experienced registered nurse, blinded to group status. To protect confidentiality of personal health information, all information collected through the data abstraction will be protected with software that encrypts the data as they are entered. No identifying information will be collected; instead, unique study numbers will be used for each individual. Separately, each study subject's unique health card number will be collected to permit future linkage with secondary data sources. All data will be uploaded weekly via a secure Internet connection to the study centre.

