**Figure 2 F2:**
[figure not shown]
**Contents of the Toolkit included (left to right): a synopsis of the guideline elements pertaining to cardiovascular disease risk, a laminated card with a simplified algorithm for cardiovascular risk management, and a pad of tear-off sheets for patients with a cardiovascular risk self-assessment tool**.

In the intervention group, the Toolkit was mailed with the Spring 2009 edition of *Canadian Diabetes*, a newsletter from the CDA which provides practical information on diagnosis and treatment issues associated with diabetes that is sent quarterly to all primary care physicians in Canada. The content of this edition of the newsletter did not pertain to cardiovascular risk screening or treatment. Both the Toolkit and *Canadian Diabetes *were packaged together in a large mailing envelope. The control group received *Canadian Diabetes *alone in its usual shrink-wrap packaging, and will receive the Toolkit with the Spring 2010 edition of the newsletter.

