### Proposed sample size

We will power the study to be able to detect an absolute 10% difference in statin prescription rates between groups, a threshold similar to the median effect size found in a systematic review of printed educational materials[25]. Even this modest improvement would be an important achievement at a population level. To have 80% power to detect this difference with alpha-error of 0.05, a sample size of 408 per group would be needed. However, this sample size must be inflated by a variance inflation factor (VIF) to ensure adequate power when taking clustering into account using generalized estimating equation models[26]. The VIF is given by VIF = 1 + (*n*-1) × ρ, where *n *is the mean cluster size and ρ is the intraclass correlation coefficient, a measure of the degree of correlation of the outcome within clusters. Previous data have shown that ρ for appropriate statin use by diabetic patients clustered within primary care physicians is 0.05[27]. If we assume a cluster size of 20 eligible patients per physician (which represents a reasonable number of patients whose data could be abstracted in two days), the VIF is 1 + 0.05 × (20-1) = 1.95, so the actual required sample size is 796 patients in each group, or 40 physicians per group.

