### Planned analyses

We hypothesize that patients whose family physicians are in the intervention arm will have greater use of appropriate medications and better achievement of targets than patients whose family physicians are in the control arm. The analysis to test this hypothesis will be carried out using multilevel hierarchical logistic regression models to account for the clustered nature of the data, i.e., patients clustering within physicians and the attendant reduction in statistical independence. The group assignment will be a physician-level variable.

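### Statin use before the mailing is to be abstracted but is undated and has no stated role in the primary analysis; adjusting for it would sharpen an otherwise sound comparison

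*Protocol article*

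**What the plan says.** All of this is in the Protocol article.

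- **Outcome** (Data collection and outcomes). Receiving a statin is "as determined by the record of a new prescription, the record of a prescription renewal, or a notation that the patient is taking a statin". On timing: "Outcome measures will be assessed for each patient for the period between July 2009 and March 2010". One reason given for the choice is that "no more than one-third of patients currently receive statins".
- **Intervention timing** (Intervention). "In the intervention group, the Toolkit was mailed with the Spring 2009 edition of" the association's newsletter, so before the outcome window opens.
- **Baseline data** (Data collection and outcomes). For each patient, "clinical information (including diabetes duration, comorbidities, family history and baseline drug utilization) will be collected". No date or event defines baseline.
- **Analysis** (Planned analyses). "The analysis to test this hypothesis will be carried out using multilevel hierarchical logistic regression models", with patients clustered within physicians and group entered at physician level. No other term is named and none is excluded.
- **Sample size** (Proposed sample size). The aim is to "detect an absolute 10% difference in statin prescription rates between groups". "To have 80% power to detect this difference with alpha-error of 0.05, a sample size of 408 per group would be needed", inflated by 1.95 to 796 patients, or 40 physicians, per group.

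**The concern.** A patient who was on a statin before the mailing and stays on it counts as a success in either arm, whatever the Toolkit does. Such patients add variance and say little about the intervention.

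Prior prescribing may also differ between two sets of 40 physicians. Chance alone can produce a difference. So can recruitment, because under Study participants the physicians are invited and agree after randomization and mailing. Any such difference passes into an unadjusted contrast.

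The variable that would deal with both problems is being collected. Its value depends on its date. If chart readers take baseline to be July 2009, the start of the outcome window, it falls after the mailing, and adjusting for it could remove part of the effect. Abstraction starts in spring 2010, so an undated field would be costly to repair across 2 × 40 × 20 = 1,600 charts.

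**Working it through.** **1. The plan's own figure.** Two-sided alpha 0.05, 80% power, 40% versus 50% (rates assumed; the article gives only the difference): 388 per group, or 408 with continuity correction. Then 408 × 1.95 = 795.6, so 796, and 796/20 = 39.8, so 40 physicians. At 33.3% versus 43.3% the need is 370, or 390 with the correction. The stated size is not short.

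**2. What 10 points overall means.** If the Toolkit affects only non-users, the difference needed among them is 10/(1 − b), where b is prior use: 12.5 points at b = 20% and 15 at b = one-third.

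**3. Chance imbalance in prior use.** Inputs: b = one-third (the article's upper figure), ICC 0.05 (the article's value for statin use, assumed to hold for prior use), 800 patients per arm.

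SD = √(2 × 0.222 × 1.95/800) = 0.033, or 3.3 points.

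An imbalance of 4.3 points or more in either direction (4.3 is the later review's median effect, given in the Discussion) has probability of about 19%. The part that reaches the outcome is roughly imbalance × (persistence − uptake): 3.3 × 0.6 = 2.0 points at 80%/20%, and 3.3 × 0.9 = 3.0 at 95%/5%.

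**4. Variance left after adjustment.** Persistence k and control uptake u are assumptions, as is an effect confined to non-users. For an overall effect d:

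- intervention-arm uptake: u + d/(1 − b)
- arm proportion: p = bk + (1 − b)u
- total variance per patient: p(1 − p)
- variance within prior-use strata: bk(1 − k) + (1 − b)u(1 − u)
- ratio: the within-strata variance summed over arms, divided by the total variance summed over arms

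Worked for b = 20%, k = 0.80, u = 0.20, d = 8.1 points. Intervention uptake is 0.20 + 0.081/0.80 = 0.301. The proportions are 0.320 and 0.401. Total 0.2176 + 0.2402 = 0.4578; within strata 0.1600 + 0.2003 = 0.3603; ratio 0.79.

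Unadjusted SE = √(0.4578 × 1.95/800) = 0.0334, and power = Φ(0.081/0.0334 − 1.96) = 0.68. Adjusted SE = 0.0334 × √0.787 = 0.0296, and power = 0.78.

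| b, k, u | Ratio at d = 0 | Ratio at 8.1 points | Power at 8.1, unadjusted to adjusted |
|---|---|---|---|
| 20%, 0.80, 0.20 | 0.74 | 0.79 | 0.68 to 0.78 |
| 33%, 0.95, 0.10 | 0.32 | 0.43 | 0.65 to 0.95 |
| 33%, 0.95, 0.05 | 0.21 | 0.33 | 0.67 to 0.98 |

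At 10 points the first row's ratio is 0.80. Over the grid the reduction is therefore about 20% to 80%, with the upper end reached only when the effect is near zero.

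**5. Simulation** (40 × 20 per arm, ICC 0.05). Over prior use 20-33%, persistence 80-95% and uptake 5-20%, power at 8.1 points rises from about 0.69-0.77 to about 0.85-0.99, with type I error near 5%. On a narrower grid (prior use 20-30%, persistence 90-95%, uptake 5-15%), power at 4.3 points rises from 26-28% to 44-79%, with type I error of 4.4-5.5%. The hand figures in step 4 are lower because they keep the full 1.95 inflation in both analyses. The narrower simulation put the ICC on prior use and on initiation separately, which gives a smaller ICC for the combined outcome.

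**The case against.** The best counter-argument is that nothing here is wrong. Current receipt is a reasonable outcome, and renewals and chart notes are how it is measured. Prior users are expected in both arms, so they dilute the contrast without biasing it, and the dilution is already inside a target set on overall prescribing rates. All of this stands. It rules out the stronger inference a reader might draw, that the outcome is invalid or the trial underpowered as planned.

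A reader might also infer that the plan has decided to leave prior use out of the model. The text does not support that. Planned analyses is one paragraph of a condensed article; it lists no covariates and excludes none, and a covariate list or data dictionary may sit in documents not shown. Nor does anything say that baseline means July 2009. What can be said is only that no role and no date are stated.

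Two further objections stand in part. Persistence and uptake are not in the document, so the gain can be given only as a range. And the simulations compared cluster means with linear adjustment, whereas the plan is multilevel logistic. There, adding a strong covariate changes the odds ratio to one conditional on prior use, so the precision figures do not transfer exactly and the estimand must be named.

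The no-bias argument does not fully cover recruitment: agreement to take part comes after allocation, so the analysed physicians are not simply the randomized ones.

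**Conclusion.** The point holds as a recommendation on efficiency and balance. The outcome and the stated sample size are sound. Adjusting for statin use before the mailing would reduce variance at every setting tried, by roughly 20% to 80%, and lift simulated power at 8.1 points from about 0.7-0.77 to about 0.85 or more (0.78 by the cautious hand calculation in the weakest case). It would also address an imbalance in prior prescribing whose chance SD is about 3.3 points.

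These sizes rest on assumed persistence and uptake, on an effect confined to non-users, and on an ICC of 0.05 for prior use. Adjustment would not make the trial reliably powered at 4.3 points. The benefit depends on baseline being fixed before the mailing.

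**What to change.** 1. Define baseline statin use as use immediately before the Spring 2009 mailing, on the same calendar date in both arms and not July 2009. State how patients with no chart record before that date are handled.
2. Prespecify it as a patient-level covariate in the primary multilevel logistic model.
3. Report a marginal risk difference beside the conditional odds ratio; this also matches the absolute scale on which the trial was powered.
4. Report new starts among patients not on a statin before the mailing as a supportive analysis.

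If the full protocol or analysis plan already does this, a sentence in Planned analyses is enough. Otherwise the cost is one dated field in an abstraction that already covers baseline drugs, one model term, and an odds ratio that must be labelled conditional. The sample size need not change.

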### Study participants

From the Toolkit's mailing lists, we will randomly select Ontario family physicians to approach about participating in a primary data abstraction study. Physicians will be contacted by fax with a brief synopsis of the study purpose and the planned data abstraction. They will be invited to accept or decline to participate by fax or telephone. Follow-up telephone calls will be made to physicians who do not respond. We will recruit 40 family physicians from each of the intervention and control arms. For practical reasons, the recruited physicians will practice within 150 km of the study centre, which incorporates both urban and rural areas. In order to increase the likelihood that the participating physicians are representative of typical practitioners and are not self-selected towards good performers with an interest in diabetes quality of care, the letter of invitation will not describe the study in detail or what data will be collected.

Individual patients with diabetes seeing each physician will be identified through the physician's billing records or electronic health records. We will randomly select from these records 20 diabetic patients per physician aged = 18 years who were seen in the office at least once between July 2009 and March 2010, and who fulfill the Clinical Practice Guidelines' definition of being at "high risk for CV events": [18]

• Men aged ≥ 45 years, women aged ≥ 50 years; or

• Men aged < 45 years and women < 50 years with at least one of the following:

• Macrovascular disease (silent myocardial infarction, or evidence of peripheral arterial, carotid arterial or cerebrovascular disease)

• Microvascular disease (nephropathy or retinopathy)

• Family history of premature coronary or cerebrovascular disease in a first-degree relative

• Extreme level of a single risk factor (LDL-C > 5.0 mmol/L, systolic BP > 180 mmHg)

• Duration of diabetes > 15 years with age > 30 years

Patients who were concomitantly seeing endocrinologists will not be specifically excluded from the study. Although such patients may be more likely to have received benefit from the Toolkit since all endocrinologists received the Toolkit in a non-randomized fashion, less than 18% of people with diabetes in Ontario see both endocrinologists and family physicians[21]. Any such patients would bias the results of the study towards the null.

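### The six intermediate outcomes use the last routine chart value, with no timing condition and no pre-mailing value named, so a valid arm comparison is open to dilution, loses precision and covers only measured patients

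*Protocol article*

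**What the plan says.** Data collection and outcomes, in the protocol article, lists six intermediate outcomes to be taken retrospectively from office charts. The observation period is fixed: "Outcome measures will be assessed for each patient for the period between July 2009 and March 2010". Within it, "When there are multiple measurements for these intermediate measures for a patient, the last one during the observation period will be used". No other timing condition is given.

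The same section describes what else is abstracted: "clinical information (including diabetes duration, comorbidities, family history and baseline drug utilization) will be collected". Drug use is the only item there labelled as baseline, and none of the six intermediate measures is named.

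Study participants admits patients "who were seen in the office at least once between July 2009 and March 2010", so one visit is enough. The Intervention section places the mailing before the window: "the Toolkit was mailed with the Spring 2009 edition of" the newsletter.

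Planned analyses compares the arms and expects "greater use of appropriate medications and better achievement of targets than patients whose family physicians are in the control arm". No endpoint defined as change from baseline is stated.

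**The concern.** Nobody schedules a follow-up measurement in this trial; values arise from usual care. Three consequences follow.

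- **Timing.** A patient's last reading may be the only one, taken early in the window. If it is high and prompts a change, it is recorded as the outcome although it precedes the response.
- **Baseline.** With no earlier value, the comparison cannot be adjusted for prior control. That matters more than usual here, because physicians are approached after allocation and may decline, so randomisation alone does not secure balance among those who take part.
- **Denominator.** The rule yields no outcome for a patient with no value in the window. The Toolkit contains a risk-assessment algorithm and a patient self-assessment pad, so it could change who gets measured.

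At stake is the target-achievement half of the hypothesis: a real benefit could be understated, or the result distorted by who was tested.

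**Working it through.** **The plan's own figure.** The article gives no sample size for the intermediate outcomes. Its clustering inputs concern statin use: intraclass correlation (ICC) 0.05 and 20 patients per physician. The inflation reproduces: 1 + 19 × 0.05 = 1.95; 408 × 1.95 = 795.6, so 796; 795.6 / 20 = 39.8, so 40 physicians per arm. That figure is not in question here. The ICC of 0.05 is borrowed below for illustration only.

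**1. Timing, from the article's own logic.** The clinical inertia measure reads: "For each A1c, blood pressure or LDL-cholesterol reading that is above the recommended clinical practice guideline target", the abstractor looks for a recommended change at the following visit. The article therefore treats a reading as coming before the response to it. Set beside a one-visit eligibility rule, this means a reading can be after the mailing yet before any action.

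Let *f* be the share of last readings that precede the response they should reflect, similar in both arms (assumed; the article gives no figure). The effect retained is 1 − *f*, and the sample needed rises by 1/(1 − *f*)².

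| *f* (assumed) | Effect retained | Sample multiplier |
|---|---|---|
| 10% | 90% | 1.23 |
| 25% | 75% | 1.78 |
| 50% | 50% | 4.0 |

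**2. Baseline adjustment.** Let *r* be the correlation between pre-mailing and follow-up value, assumed 0.5 to 0.7. In a linear approximation with total variance 1, the variance of a physician mean is 0.05 + 0.95/20 = 0.05 + 0.0475 = 0.0975. The within-physician share is 0.0475/0.0975 = 0.487.

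- If adjustment explains only within-physician variance, the reduction is 0.487 × *r*²: 0.487 × 0.25 = 12% and 0.487 × 0.49 = 24%. The equivalent sample is 1/(1 − 0.12) = 1.14 to 1/(1 − 0.24) = 1.32 times larger.
- If it explains physician-level variance equally well, the reduction is *r*²: 25% to 49%, equivalent to 1/0.75 = 1.33 to 1/0.51 = 1.96 times the sample.

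The earlier value should enter as a covariate, not through a change score. The change-score variance relative to follow-up only is 2(1 − *r*), which is 1.0 at *r* = 0.5 (no gain) and 1.4 at *r* = 0.3 (a loss).

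**3. Denominator (illustration, every input assumed).** Suppose 70% of controls have an LDL value with mean 2.4 mmol/L, and the Toolkit leads to 10 to 15 points more patients being tested, whose mean is 3.0, with no change in treatment.

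- 10 points more: (0.70 × 2.4 + 0.10 × 3.0)/0.80 = 2.475, a difference of 0.08.
- 15 points more: (0.70 × 2.4 + 0.15 × 3.0)/0.85 = 2.506, a difference of 0.11.

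If the additional patients also averaged 2.4, the difference would be zero; if lower, its sign would reverse.

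**The case against.** The strongest reply is that this is a randomised comparison of values recorded after the mailing, and no baseline is needed to estimate it. That stands. A reader might infer that the plan cannot measure any change at all. The documents do not support that: the stated hypothesis is a contrast between arms, and only within-patient change and baseline adjustment are not provided for. Taking the last value also favours the latest reading available.

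A reader might likewise infer that most patients have a single reading, or that newly tested patients would appear in the intervention arm alone. Neither has a source. The article sets a minimum of one visit and says nothing about how often patients are measured, and control physicians also start testing patients.

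The list of abstracted items is introduced as a set of inclusions, so earlier values are not ruled out, and an article commonly leaves covariates and missing-data handling to fuller documents. This is a fair limit on the point: silence on the analysis is not the fault. What remains is the outcome rule that the article does fix, and a named list that gives the drug outcomes a baseline counterpart but none for the other six.

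The inertia outcome partly covers the trigger-reading problem, for A1c, blood pressure and LDL-cholesterol. It captures the physician's response, not the later level. Finally, the precision formula is for linear models, whereas Planned analyses specifies multilevel logistic models, so the gain does not carry over directly.

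**Conclusion.** The point holds as a worthwhile design improvement for secondary outcomes, not as an error that invalidates the comparison. Every outcome value is post-mailing, but not necessarily after the treatment response. With similar timing in both arms, the result is dilution toward the null, of a size that depends on an unknown *f*.

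The precision forgone is about 12-24% of the variance if adjustment works only within physicians at an ICC of 0.05, and up to 25-49% if it also explains physician-level differences equally well. Both ranges assume *r* = 0.5 to 0.7, a linear approximation and complete baseline values; missing ones would lower the gain.

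Selective measurement is possible in either direction, and the documents do not allow its size to be estimated. The primary statin outcome and its sample size are untouched.

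**What to change.** Before chart abstraction starts in spring 2010:

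1. For each of the six measures, abstract the last value before the Spring 2009 mailing, with its date. Use it as a covariate in the multilevel models, with an indicator for missing values.
2. Record the date of the follow-up value, so that its timing can be described by arm.
3. Report the proportion of sampled patients measured, by arm, for each outcome.
4. For measures with a guideline target, analyse *measured and on target* over all sampled patients beside the measured-only result. The two belong together, because more testing alone can raise the first.

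Restricting the outcome to readings from the later part of the window is not advisable. It would discard patients measured only earlier and worsen the selection problem.

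The cost is about six further values with dates per chart. Over 80 physicians × 20 patients = 1,600 charts, that is roughly 9,600 values, in charts that are already open. Abstraction takes somewhat longer, which matters because Proposed sample size ties 20 patients per physician to two days' work. Some earlier values will be missing. Adding the fields now avoids returning to 80 offices later.

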**Design:**

A pragmatic cluster-randomized trial will be conducted to evaluate the CDA's CVD Toolkit. All family physicians in Ontario, Canada were randomly allocated to receive the Toolkit, which includes several printed educational materials targeting CVD screening, prevention and treatment, either in spring 2009 (intervention arm) or in spring 2010 (control arm). Randomization occurred at the level of the practice. Forty family physicians from each arm will be recruited to participate, and the medical records for 20 of their diabetic patients at high risk for CVD will be retrospectively reviewed. Outcome measures will be assessed for each patient between July 2009 and March 2010. The primary outcome will be that the patient is receiving a statin. Secondary outcomes will include 1) the receipt of an angiotensin converting enzyme inhibitor or angiotensin receptor blocker, 2) various intermediate measures (A1c, blood pressure, LDL-cholesterol, total-/HDL-cholesterol ratio, body mass index and waist circumference), and 3) clinical inertia (the failure to change therapy in response to an abnormal A1c, blood pressure or cholesterol reading). The analysis will be carried out using multilevel hierarchical logistic regression models to account for the clustered nature of the data. The group assignment will be a physician-level variable. In addition, a process evaluation study with six focus groups of family physicians will assess the acceptability of the CDA's Toolkit and will explore factors contributing to any change or lack of change in behaviour, from the perspectives of family physicians.

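### The clinical-inertia rule looks for a response only at the next visit, so action taken at the visit of the reading or between visits can be scored as inertia

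*Protocol article*

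**What the plan says.** The rule is in the protocol article under Data collection and outcomes. The trigger is a single reading: "For each A1c, blood pressure or LDL-cholesterol reading that is above the recommended clinical practice guideline target". For each one, "we will determine whether, at the next patient visit, there is notation in the chart of a recommended change". The listed changes are "the addition of a new medication, a dose change for an existing medication, a dietary or physical activity recommendation, etc". The same section fixes the period: "Outcome measures will be assessed for each patient for the period between July 2009 and March 2010". Under Study participants, a patient qualifies with a single office visit in that period.

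The abstract (Design) lists the outcome third among the secondary outcomes and describes it as "clinical inertia (the failure to change therapy in response to an abnormal A1c, blood pressure or cholesterol reading". It gives no time window, does not mention lifestyle advice, and refers to cholesterol where the body specifies LDL-cholesterol.

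**The concern.** Inertia means that an abnormal value drew no response. A rule that measures it must search every point at which a response could occur. This one names only the visit after the reading.

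The gap matters most for blood pressure, because the reading is available while the patient is still in the room. A drug added that day is the opposite of inertia. If the next note records nothing further, the rule as written scores it as inertia. The same applies to a change made between visits, for example by telephone once a laboratory result arrives.

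Two smaller problems sit beside this:

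- A reading at a patient's last visit in the window has no next visit inside it, and the text does not say what becomes of that reading.
- The abstract and body can classify the same chart differently when the only response is dietary or activity advice. The open-ended end of the body's list leaves the abstractor to decide what else qualifies.

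At stake is whether this outcome can show the effect it was chosen to show. The Toolkit includes a laminated card with a simplified algorithm, and the Discussion expects it to be more actionable than materials that only urge change. Action at the visit itself is a plausible way for it to work.

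**Working it through.** The protocol gives no figure for inertia, so there is none to reproduce. The check compares the texts and then illustrates size with assumed rates.

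**1. How the rule scores each case, read literally**

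| Response in the chart | Real response? | Score under the body's rule |
|---|---|---|
| Drug changed at the visit of the reading, not noted again | Yes | Inertia |
| Drug changed between visits, not noted at the next visit | Yes | Inertia |
| Drug changed at the next visit | Yes | Response |
| Only diet or activity advice, at the next visit | Yes under the body; unclear under the abstract | Response |
| No action, no later visit in the window | Not known | Not stated |

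The first two rows are the defect. The fourth is the mismatch between abstract and body. The fifth is an unstated denominator.

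**2. Dilution when the same share is missed in both arms**

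Let a be the proportion of abnormal readings truly acted on, and s the share of those actions that the rule misses. Then

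- true inertia = 1 − a
- measured inertia = 1 − a(1 − s)
- measured arm difference = true difference × (1 − s)

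Assume a = 50% in control and 60% in intervention:

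| s | Control | Intervention | Difference (points) |
|---|---|---|---|
| 0% | 50.0% | 40.0% | 10 |
| 25% | 62.5% | 55.0% | 7.5 |
| 50% | 75.0% | 70.0% | 5 |
| 75% | 87.5% | 85.0% | 2.5 |

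For example, at s = 50%: 1 − 0.5 × 0.5 = 75.0% and 1 − 0.6 × 0.5 = 70.0%.

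**3. If the Toolkit moves action to the visit of the reading**

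Let d be the probability of action at the visit of the reading, and x the probability of a noted change at the next visit, independent of d. True inertia is (1 − d)(1 − x). The rule records 1 − x, which does not depend on d. Assume d is 20% in control and 30% in intervention, with x the same in both arms:

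- x = 10%: true inertia is 0.8 × 0.9 = 72% v 0.7 × 0.9 = 63%, a fall of 9 points. Recorded: 90% v 90%.
- x = 20%: true inertia is 0.8 × 0.8 = 64% v 0.7 × 0.8 = 56%, a fall of 8 points. Recorded: 80% v 80%.

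Here a real benefit is recorded as no difference.

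**The case against.** **Laboratory values.** A1c and LDL-cholesterol results usually arrive after the visit at which they are ordered, so the next visit is a sensible first opportunity to respond. That is general reasoning, since the document does not say when results are available, but it stands. For these two measures the gap is limited to changes made between visits. Blood pressure is the main problem.

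**The text does not say "only".** It does not state that same-visit action scores as inertia, and the abstractor's manual may be more generous. This is fair: the consequence is inferred. But the article does fix a time point, and it is too narrow if followed.

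**Abstract against body.** The abstract is silent on timing, so it cannot contradict the body there. Lifestyle advice can also be called therapy. What remains is a difference in wording about what counts as a change, which needs aligning. Making medication change the sole definition would be a preference.

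**Readings with no next visit.** These may simply be left out. That is mainly a denominator detail, but changing the window means settling it.

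Two stronger readings are tempting and should not be drawn:

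- *That the Toolkit would appear to cause inertia.* In step 3 the recorded difference is zero, not reversed. With x the same in both arms, a reversal needs the further assumption that action at one visit makes a noted change at the next less likely. The documents give no rates to support that.
- *That repeated readings per patient make the p-values too small.* The unit is the reading, while Planned analyses describes "patients clustering within physicians and the attendant reduction in statistical independence". But group is a physician-level variable, so the arm effect is tested against variation between physicians, and a physician random effect absorbs the correlation within patients below it. Null simulations with only a physician intercept (1,000 runs per scenario, 40 physicians per arm, 20 patients each, 2 to 4 readings per patient or a number varying from 0 to 8, assumed within-patient correlation 0.1 to 0.3) rejected in 4.9% to 5.4% of runs at a nominal 5%. That is within simulation error.

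**Conclusion.** The concern holds as a defect in the scoring rule of one secondary outcome. Read literally, the rule misses responses made at the visit of a blood pressure reading, and those made between visits, unless they are noted again at the next visit. Measured inertia is then too high in both arms.

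If a share s of true responses is missed equally in both arms, the arm difference shrinks by 1 − s. If the Toolkit increases action at the visit of the reading, the error can work against it; under the assumptions in step 3, a true fall of 8 to 9 points is recorded as zero. All the rates are assumed, so the direction of the dilution is firmer than its size.

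The definition of a change also differs in wording between abstract and body and should be reconciled. The primary statin outcome and the sample size do not use this rule and are unaffected.

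**What to change.** Before abstraction starts in spring 2010, revise the abstraction rule:

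1. Score a response if a change is recorded at any time from the date of the reading, inclusive, through the next visit. State this separately for blood pressure and for laboratory values, and say that changes between visits count.
2. Say what happens to readings with no later visit in the window. The cleaner choice is to score only readings that have one. The alternative is to treat readings with no recorded action and no next visit as not evaluable. That keeps unfollowed readings only when they were acted on, so it lowers measured inertia; if used, report the number excluded by arm.
3. Use one definition in the abstract and body, including whether cholesterol means LDL-cholesterol only. Replace the open-ended list with a closed one. Recording medication change and lifestyle advice as separate components would let either definition be reported.

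The cost is a revised abstraction form and training for the nurse abstractor. No extra charts or visits are needed. Making the change after abstraction could mean returning to up to 80 offices (40 physicians in each of two arms).
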